**7.0 STUDY PROCEDURES/EVALUATIONS**

**7.1 Clinical Evaluations and Procedures**

See Appendix I for a complete Schedule of Procedures and Evaluations by study visit.

Interested volunteers will contact the study staff to discuss study details, including inclusion criteria, prior to the screening visit. Potential participants will be screened for presumptive eligibility for the study according to the procedures described below. All procedures will be completed in a step-wise manner for potential participants who meet the study eligibility criteria. For participants who do not meet the eligibility criteria, screening will be discontinued when ineligibility is determined. For potential participants who are found to be presumptively eligible at this visit, final eligibility will be confirmed at an Enrollment Visit scheduled to take place 2-6 days following the next menses within 30 days of the Screening Visit.

## Clinical Procedures

- Obtain informed consent.
- Assign Participant ID.
- Collect demographic and locator information.
- Collect sexual history.
- Collect medical history and concomitant medication information.
- Provide HIV/STI pre-test counseling.
- Collect blood for pregnancy test, HIV EIA, RPR, herpes serology, hepatitis B surface Ag, hepatitis B core IgM and IgG.
- Collect blood for progesterone and estradiol, liver and kidney function.
- Collect urine for HCG pregnancy test; provide participant with result.
- Collect urine for microscopy and culture.
- Perform pelvic examination including:
- Speculum examination of vagina and cervix,
- Collection of pH sample from the vaginal wall
- Swab from anterior or lateral fornix for wet prep (two samples of discharge on slide for saline prep, potassium hydroxide prep and whiff test), and PSA-specific membrane test for semen (One-Step ABA card PSA, Abacus Diagnostics, West Hills, CA)
- Collection of baseline CVL,
- Pap smear (if documentation of a negative result within the past year is not available),
- Cervical swab (DNA probe) for *N. gonorrhoeae* and *C. trachomatis*,
- If ulcerative lesions are noted, collect swab for herpes simplex virus culture,
- Bimanual exam for adnexal masses or tenderness.
  - If participant determined to be ineligible, end visit and complete all required data collection forms. If participant remains presumptively eligible, schedule Enrollment Visit to occur 2-6 days following menses within 30 days after the Screening Visit.
- Instruct participant not to use vaginal products and to abstain from sexual intercourse for 48 hours prior to the Enrollment Visit.
- Complete all required data collection forms.

### Laboratory Procedures

- Record results of serum and urine pregnancy tests.
- Record results of urine microscopy and culture.
- Record vaginal pH measurement.
- Examine wet mount by direct microscopy to detect *T. vaginalis*, *C. albicans* infections, and clue cells for BV. Perform whiff test.
- Conduct PSA-specific membrane test for semen.
- Conduct tests for *N. gonorrhoeae* and *C. trachomatis*.
- Read and record Pap smear results.
- Conduct culture of swab for HSV, if clinically indicated.
- Conduct serology for RPR with confirmation by FTA-ABS or TPHA for *T. pallidum.*
- Conduct type-specific herpes serology.
- Conduct EIA test for HIV.
- Measure progesterone, estradiol, liver and kidney function.
- Process, spin, aliquot and freeze CVL supernatant for cytokines.
- Stain cell pellets with monoclonal antibodies against leukocyte phenotypic antigens for CD45 (hematopoietic cells), CD19 (B cells), CD3, CD4, CD8 (T cells), CD14 (macrophages) and CD11 (dendritic cells) and analyze by seven-color FACS.
- Measure IgG, IgA, IL-1, IL-1, IL-2, IL-6, IL-8, IL-10, IL-12, IFN-, IFN-, TNF-, MIP-1, MIP-1, RANTES, SLPI, TGF-, IL-1ra.
- Measure HNP1-3, HD-5, HD-6, hBD-1, hBD-2, hBD-3 and lactoferrin.
- Measure total protein concentration in CVL (BCA, Pierce).
- Evaluate anti-viral and anti-bacterial activity.

Enrollment Visit (Day 0)

Participants who are found to be presumptively eligible at their Screening Visits will complete Enrollment Visits within 30 days after the Screening Visit. In order to ensure a minimum of 21 days without menstrual bleeding, participants will be scheduled for an Enrollment Visit 2-6 days after the next menstrual period ends. Participants who do not complete an Enrollment Visit within 30 days of screening must repeat the screening process in order to participate. All participants will receive their screening test results at their Enrollment Visits. For those whose test results meet the study eligibility criteria, the procedures below will be undertaken in a step-wise manner to confirm eligibility. As was the case at the Screening Visit, the procedures will be discontinued if ineligibility is determined at this visit.

## Clinical Procedures

- Update locator information.
- Review interim sexual history, medical history and concomitant medication information.
- Provide participant with screening test results.
- Provide HIV/STI test results and post-test counseling.
- Collect urine for HCG pregnancy test; provide participant with result.
- Perform pelvic examination including:
- Speculum examination of vagina and cervix,
- Collect pH sample from the vaginal wall,
- Gently swab anterior or lateral fornix for wet prep (two samples of discharge on slide for saline prep, potassium hydroxide prep, whiff test, and microscopic inspection for sperm) and PSA-specific membrane test for semen,
- CVL collection.
- If ulcerative lesions are noted, collect swab for herpes simplex virus culture.
- If patient determined to be ineligible, end visit and complete all required data collection forms. If participant remains eligible, randomize/assign Enrollment ID and continue.
- Collect blood for progesterone, estradiol and tenofovir levels.
- Distribute study supplies, including sixteen (16) single-application tubes of 1% tenofovir gel or matched placebo gel and 16 single-use applicators, application and storage instruction sheet (Appendix III) and panty liners.
- Distribute Participant Diary
- Provide information regarding product administration.
- Provide guidance for the administration of the first dose of study gel by the participant.
- Instruct participant on anticipated amount, consistency and color of discharge due to gel expulsion.
- Instruct participant on proper gel insertion techniques and supply storage.
- Instruct participant to apply each daily dose at bedtime starting the next night.
- Schedule Day 3 Study Visit. Instruct participant not to apply the Day 3 dose until after the Study Visit.
- Complete all required data collection forms and record any AE information.

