Fourteen of 25 women (56%) with pharmacokinetic (pK) results had low, but detectable, serum tenofovir levels (limit of quantitation: 3.0 ng/ml) at some point in the 12 hours after dosing on either Day 0 (following the first dose) or on Day 13 (after daily dosing); three of the 14 had detectable levels on both days. The maximum tenofovir concentrations (Cmax) ranged from 3.0 to 25.8 ng/ml; no clear dose-concentration relationship was identified. For the woman with the 25.8 ng/ml level, this peak level occurred 2 hours following the dose; the level rapidly declined to 10.8 ng/ml at 4 hours and was undetectable at 12 hours following the dose. Besides the outlier with the highest tenofovir level, the next highest Cmax was 7.1 ng/ml. Considering all women in the pK cohort, the median tenofovir Cmax was 3.4 ng/ml (interquartile range: below limit of quantitation [3.0 ng/ml] to 4.7 ng/ml). The median Cmax for all subjects (3.4 ng/ml) corresponds to approximately 1% of the maximum (Cmax, ss) and 7% of the minimum (C24 single dose) blood concentrations at steady state with 300 mg daily oral tenofovir dosing. No clinically significant systemic toxicity was detected. These findings suggest that tenofovir 1% gel used twice daily is well tolerated in abstinent and sexually active HIV uninfected and HIV-infected women, with limited, but detectable, systemic absorption [11].

There is a theoretical risk that tenofovir absorbed systemically following intravaginal application of tenofovir gel could result in mutations of the HIV virus in participants who become infected with HIV during the study, although the risk of developing resistance to tenofovir via the K65R mutation is significant less than that observed with drugs such as lamivudine. Moreover, resistance data from the HPTN 050 study showed that no new resistance mutations evolved in plasma or cervicovaginal lavage specimens after 14 days of tenofovir gel use [11]. No participant had high-level tenofovir mutations (e.g., K65R). It should be noted, however, that a recent *in vitro* study demonstrated that tenofovir can rapidly select K65R in subtype C viruses, which prevail in Africa and Asia, but not subtype B, the subtype most common in the United States [27]. This study will enroll low-risk, HIV-negative women in the United States. Therefore, resistance should not be an issue.

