CVL will also be assayed for intrinsic anti-HSV activity. Human cervical epithelial cells (CaSki) will be treated with each CVL sample (diluted 1:2 in serum-free media) for 1 h and then challenged with serial dilutions of HSV-2(G) in triplicate. The viral titer (pfu/well) in the presence of each CVL sample or control buffer will be determined by counting plaques 48 h pi. The effects of CVL pre- and post-application of tenofovir or placebo gel on the growth of *Escherichia coli* ML-35 and *Staphylococcus aureus* will also be examined. Stationary phase bacterial cells will be washed 3 times with PBS (pH 7.4) and 10 µl of 2 X 109 CFU/ml (2 X 107 CFU) will be incubated with an equivalent volume of CVL or control fluid (1.5 mg/ml BSA in saline containing the same concentrations of penicillin and streptomycin as CVL) at 37C for 2 h. Aliquots of bacteria will be removed, subjected to sequential serial dilutions with PBS and further diluted into 5 ml of a 43C solution of 1% agarose in PBS and 1% trypticase soy broth. After rapid dispersion of bacteria, the bacteria-containing 5 ml agar sample will be poured over a trypticase soy agar underlay. Colonies will be counted using ImageQuant TL v2005 after an overnight incubation at 37C and relative number of colonies will be compared.

Given that systemic tenofovir absorption occurred in the Phase I HPTN 050 trial, tenofovir levels will be measured in serum, CVL supernatants and CVL cell pellets following repeated application of 1% tenofovir gel or matched placebo. Blood samples will be collected in potassium EDTA tubes and plasma will be separated by low speed centrifugation for 15 minutes at 4C. Plasma will be carefully transferred to sterile cryovials and stored at -70C until analysis. Plasma and CVL tenofovir levels will be quantified using an optimized solid-phase extraction procedure combined with a rapid reverse-phase high-performance liquid chromatography method and photodiode array detection. This accurate and sensitive method has been validated in human blood plasma [28]. The high extraction efficiency (98.6%), low limit of quantification, and wide linear dynamic range (10-10,000 ng/ml) make this a suitable method for use in a clinical trial. This method has been used previously on cervicovaginal fluid, which was collected via direct aspiration with a vaginal aspirator. It has not been validated in CVL to the same extent as the plasma assay.

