## Clinical Procedures

- Update locator information.
- Review interim sexual history, medical history, AE information, and concomitant medication information.
- Review daily study records, note the time of last application of the product, and conduct adherence review.
- Count and record the number of used and unused tubes and dispose of used tubes in accordance with the guidelines.
- Collect blood to measure serum tenofovir levels.
- Perform speculum exam including
- Visual inspection of vagina and cervix,
- pH sample from vaginal wall,
- Swab for wet prep and PSA-specific membrane test, and
- CVL collection.
- If abnormalities are noted, refer to Appendix IV for procedures to be followed.
- Schedule Study Visit for Day 7 and complete all required data collection forms.
- Review applicator instructions, remind participant to abstain from sexual intercourse and remind participant to continue bedtime dosing.
- Instruct participant not to apply the Day 7 dose until after the Study Visit.

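### No serum tenofovir sample is planned in the early hours after a dose, so absorption of the size seen in Phase I would mostly read below quantitation

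*Protocol*

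**What the plan says.** Protocol 4.1 gives the reason for the measurement: "Given that systemic tenofovir absorption occurred in the Phase I HPTN 050 trial, tenofovir levels will be measured in serum". Sections 3.2 and 10.1 make it an exploratory objective, and 3.2 words it as concentration after repeated daily application. Section 2.4 links systemic absorption to two named risks, hepatitis B rebound and HIV resistance mutations.

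Appendix I lists five serum tenofovir samples: Days 0, 3, 7, 14 and the Final Visit.

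- **Day 0 (7.1, Enrollment Visit).** The draw, "Collect blood for progesterone, estradiol and tenofovir levels", comes after randomization but before supplies are distributed and before "Provide guidance for the administration of the first dose of study gel by the participant". The introduction to the visit says "the procedures below will be undertaken in a step-wise manner to confirm eligibility". No second draw is listed that day.
- **Days 3, 7 and 14.** The woman's own doses are at night: "Instruct participant to apply each daily dose at bedtime starting the next night". For the next two visits the dose is held back: "Instruct participant not to apply the Day 3 dose until after the Study Visit" and "Instruct participant not to apply the Day 7 dose until after the Study Visit". No such instruction is written for Day 14, but the Day 7 list tells her to go on dosing at bedtime.
- **Final Visit.** The target is Day 21, and the visit is booked 3 to 8 days after the Day 14 visit.

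For the woman with the highest Phase I level, 25.8 ng/ml at 2 h, Section 2.3 reports that "the level rapidly declined to 10.8 ng/ml at 4 hours and was undetectable at 12 hours following the dose".

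**The concern.** By the written schedule, the five samples are one pre-dose, three next-day and one after dosing has ended. None is tied to an interval after a dose. The protocol's own background puts the detectable serum levels within 12 h of dosing and the highest at 2 h. A set of values below quantitation would therefore be the expected result even if absorption were as large as in Phase I, and it could be taken as a finding that the gel is not absorbed. The assay adds to this: 4.1 gives its linear range as 10 to 10,000 ng/ml, whereas the Phase I levels were read against a limit of 3.0 ng/ml.

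**Working it through.** **Inputs (Protocol 2.3 unless noted).** Detectable in 14 of 25 women within 12 h of dosing, on Day 0 or Day 13; limit 3.0 ng/ml. Highest woman: 25.8 ng/ml at 2 h, 10.8 at 4 h, undetectable at 12 h. Second highest Cmax 7.1, median 3.4. The median is put at about 1% of the oral steady-state maximum and 7% of the oral 24 h level. Assay range from 10 ng/ml (4.1). Tenofovir arm: 12 women (10.3).

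**Plan's own figure.** 14/25 = 56%, as stated. Section 2.4 gives the denominator as 24; this hardly matters below.

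**Decline in the highest woman, exponential through the two points.**
- k = ln(25.8/10.8)/2 = 0.435 per h; half-life = 0.693/0.435 = 1.6 h.
- Falls below 10 ng/ml at 2 + ln(25.8/10)/0.435 = 4.2 h.
- Falls below 3.0 ng/ml at 2 + ln(25.8/3.0)/0.435 = 6.9 h.
- At 12 h: 25.8 × exp(−0.435 × 10) = 0.33 ng/ml, consistent with undetectable.
- A peak of 7.1 at the same rate falls below 3.0 after ln(7.1/3.0)/0.435 = 2.0 h.

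**Slowest decline her data allow.** From 10.8 at 4 h to just under 3.0 at 12 h: half-life = 8 × 0.693/ln(10.8/3.0) = 4.3 h. At 9 h she would then be at 10.8 × 0.5^(5/4.3) = 4.8 ng/ml, above 3.0 but below 10.

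**When next-day samples fall.** Clock times are not given. Assuming bedtime at 22:00–24:00 and visits at 09:00–16:00, samples come 9 to 18 h after the dose.

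**How large absorption must be to be seen.** The 2 h level needed to read 10 ng/ml at time t is 10 × 2^((t−2)/half-life).

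| Half-life | t = 12 h | t = 16 h |
|---|---|---|
| 1.6 h | about 780 | about 4,470 |
| 4.3 h | about 50 | about 96 |
| 8 h | about 24 | about 34 |

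The 8 h row is a rough value from the implied oral levels: maximum 3.4/0.01 = 340 and 24 h level 3.4/0.07 = 49 ng/ml, so 22 × 0.693/ln(340/49) is about 8 h. A sustained level near 49 ng/ml is well above 10 and would be detected.

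**Effect of the assay floor with perfect timing.** One of 25 women peaked at or above 10 ng/ml. Expected number among 12: 12/25 = 0.48. Chance of at least one: 1 − (24/25)^12 = 39% (with 24 women, 1 − (23/24)^12 = 40%). A single 2 h draw would probably do no better, because Cmax is the maximum over several times and up to two days.

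**The case against.** Several counter-arguments have force.

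- **A reader might infer that absorption would read as absent whatever its true size.** The documents do not support that: oral-scale, sustained absorption would be measurable the next day. The blind spot is low-level absorption of the kind seen in Phase I.
- **A reader might treat this as purely a timing fault.** It is not. The 10 ng/ml floor lies above every Phase I peak but one, so a contrast between no detections here and 14 of 25 there is not what retiming would recover.
- **An early sample is not impossible.** Section 4.0 says bedtime is preferred, the Day 3 text lets a visit go ahead after same-day dosing, and no hold is written for Day 14. Such samples would arise by chance, not by plan.
- **The Day 0 order is inferred.** It rests on list position. The step-wise wording concerns confirming eligibility, and the draw comes after that decision. Still, nothing in the list places a draw after the dose.
- **The kinetics come from one woman, whom the protocol calls an outlier.** This stands. With the slower half-life she could exceed 3.0 ng/ml at 9 h, so one cannot say that even she would certainly be missed at that limit.
- **Dose times are already captured.** The diary and the Day 3, 7 and 14 visit lists record the last application.
- **The stakes are limited.** The aim is exploratory and no test or stopping rule depends on it. The protocol already treats absorption as established, excludes women with hepatitis B and plans no claim of zero absorption.

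**Conclusion.** The point holds in limited form. No serum sample is planned in the hours when the cited study found its highest level. Absorption of Phase I size would mostly fall below quantitation at next-day visits, so values below the limit would not show that absorption is absent. The stated assay range makes this worse: with 10 ng/ml as the working limit, even well-timed samples give about a 39% chance of any detection among 12 women.

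This rests on the assumed visit times, on a decline taken from one woman (half-life between 1.6 and 4.3 h), on 10 ng/ml serving as the limit because 4.1 states no figure for it, and on Phase I levels carrying over. The Phase I study mixed gel strengths and once- and twice-daily use, although it found no clear dose-concentration relation. The matter is worth correcting because the change is cheap, but the gain is modest for an exploratory objective.

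**What to change.** 1. In 7.1 (Enrollment Visit), move the existing Day 0 draw, with progesterone and estradiol so that there is still one needle stick, to about 2 h after the supervised first dose. The placebo arm is the negative control. Cost: no extra tube or assay, but a wait of about 2 h, loss of each woman's own pre-dose sample, and a value that reflects a single dose while the objective concerns repeated dosing. In Phase I only three of the 14 women with detectable levels had them on both days, so a Day 0 value is a weak stand-in for later use.
2. Report the Day 3, 7 and 14 serum values by the time since last application that is already recorded. State in 3.2 and 10.1 that they are next-day levels and that values below quantitation are not evidence of no absorption. Cost: wording only.
3. In 4.1, state the assay's lower limit of quantitation in plasma and set it beside the Phase I levels (median Cmax 3.4, second highest 7.1, highest 25.8 ng/ml). If it is 10 ng/ml, say that retiming alone does not make Phase I-scale absorption measurable. Cost: one sentence.

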## Laboratory Procedures

- Record results of urine pregnancy test.
- Record vaginal pH measurement.
- Examine wet mount by direct microscopy to detect *T. vaginalis*, *C. albicans* infections, clue cells for BV, and/or sperm and record results. Perform whiff test and record results.
- Conduct PSA-specific membrane test for semen.
- Measure progesterone, estradiol and tenofovir levels.
- Process, spin, aliquot and freeze CVL supernatant for cytokines.
- Stain cell pellets with monoclonal antibodies against leukocyte phenotypic antigens for CD45 (hematopoietic cells), CD19 (B cells), CD3, CD4, CD8 (T cells), CD14 (macrophages) and CD11 (dendritic cells) and analyze by seven-color FACS.
- Measure IgG, IgA, IL-1, IL-1, IL-2, IL-6, IL-8, IL-10, IL-12, IFN-, IFN-, TNF-, MIP-1, MIP-1, RANTES, SLPI, TGF-, IL-1ra.
- Measure HNP1-3, HD-5, HD-6, hBD-1, hBD-2, hBD-3 and lactoferrin.
- Measure total protein concentration in CVL (BCA, Pierce).
- Evaluate anti-viral and anti-bacterial activity.
- Measure tenofovir level in CVL supernatant and cell pellet.

## Follow-up Visit (Day 3)

A subsequent visit will be scheduled after 2-4 days of product dosing (target Day 3 which is after 3 doses of drug or placebo). Every attempt will be made to schedule the appointment after 3 days of dosing. If a participant has discolored or malodorous vaginal discharge or suspected cervicitis at any Study Visit, an appropriate clinical and laboratory work-up will be conducted (see Appendix IV). If a participant has a genital ulcer, tests will be conducted for syphilis or herpes simplex as appropriate. Continuation in the study will be based on the severity of the abnormality noted as described in Appendix IV. If a participant applies the drug or placebo on the day of the study visit instead of at bedtime, the time of usage will be recorded and the study visit will be performed as scheduled.

## Clinical Procedures

- Update locator information.
- Review interim sexual history, medical history, AE information, and concomitant medication information.
- Review daily study records, note the time of last application of the product, and conduct adherence review.
- Count and record the number of used and unused tubes and dispose of used tubes in accordance with the guidelines.
- Collect blood to measure serum tenofovir levels.
- Perform speculum exam including
- Visual inspection of vagina and cervix,
- pH sample from vaginal wall,
- Swab for wet prep and PSA-specific membrane test, and
- CVL collection.
- If abnormalities are noted, refer to Appendix IV for procedures to be followed.
- Schedule Study Visit for Day 7 and complete all required data collection forms.
- Review applicator instructions, remind participant to abstain from sexual intercourse and remind participant to continue bedtime dosing.
- Instruct participant not to apply the Day 7 dose until after the Study Visit.

## Laboratory Procedures

- Record vaginal pH measurement.
- Examine wet mount by direct microscopy to detect *T. vaginalis*, *C. albicans* infections, clue cells for BV, and/or sperm. Perform whiff test and record results.
- Conduct PSA-specific membrane test for semen.
- Measure serum tenofovir levels.
- Process, spin, aliquot and freeze CVL supernatant for cytokines.
- Stain cell pellets with monoclonal antibodies against leukocyte phenotypic antigens for CD45 (hematopoietic cells), CD19 (B cells), CD3, CD4, CD8 (T cells), CD14 (macrophages) and CD11 (dendritic cells) and analyze by seven-color FACS.
- Measure IgG, IgA, IL-1, IL-1, IL-2, IL-6, IL-8, IL-10, IL-12, IFN-, IFN-, TNF-, MIP-1, MIP-1, RANTES, SLPI, TGF-, IL-1ra.
- Measure HNP1-3, HD-5, HD-6, hBD-1, hBD-2, hBD-3 and lactoferrin.
- Measure total protein concentration in CVL (BCA, Pierce).
- Evaluate anti-viral and anti-bacterial activity.
- Measure tenofovir level in CVL supernatant and cell pellet.

